#### 4.2.3. Exclusion Criteria

Patients who meet any of the following will be excluded: (1) with congenital or rheumatic heart disease or severe cardiopulmonary insufficiency (grades 3 and 4 of cardiac function), or uncontrolled severe arrhythmias (including ventricular tachycardia, supraventricular tachycardia), or not controlled hypertension (systolic blood pressure ≥ 160 mmHg or diastolic blood pressure ≥ 100 mmHg), (2) with cerebrovascular disease, or with severe liver and kidney dysfunction, or with endocrine, urinary, blood system, and other serious primary diseases, (3) within 4 weeks, having a history of major organ surgery such as head, chest, or abdomen or bleeding tendency, (4) those who have taken hypoglycaemic agents or glucocorticoids, thiazide diuretics, and other drugs that affect blood sugar levels within 3 months, (5) people with diseases affecting blood glucose metabolism, such as thyroid glands and adrenal diseases, or those with previous history of the aforementioned diseases, (6) allergies or persons allergic to known ingredients of the studied drug, (7) pregnant and lactating women or those with a pregnancy plan, and (8) subjects who participated in other clinical trials in the last 3 months. Researchers consider that subjects should not participate in clinical trials.

### 4.3. Interventions

All subjects participating in the trial will continue to receive basic medicine. Subjects will take random oral Ginkgo biloba pills or Ginkgo biloba drop pills simulant at each period, three times a day, five at a time.

### 4.4. Drug Inventory

At each follow-up visit, the drug administrator will record the amount of the drug accepted, taken, and returned by the subject as a matter of fact to determine the adherence of the subject and record it in a timely manner. Subject medication compliance = (dosage amount - not used)/dose should be×100%.

### 4.5. Randomization

With the help of statisticians at Xiyuan Hospital of China Academy of Chinese Medical Sciences, this test will use block randomization, and with a block size of 2. The sequence of test drugs is applied by the SAS random program to generate a “test drug random coding table.” The test drugs were randomly assigned by the database administrator according to the coding table. The prepared research drugs will be delivered, stored, and distributed in the pharmacy of Xiyuan Hospital Clinical Pharmacology Institute. Patients and investigators were blinded to all randomization and packaging procedures until completion of trial. And each subject was randomly assigned to three matched treatment groups, such as BA-AB-BA or AB-BA-BA, in the order in which they were treated.  Figure 1 shows the flow of participants through the trial.

### 4.6. Blinding

During the trial, the blinding method will be strictly applied to the investigator and the subject. The personnel who did not directly participate in the trial will be randomly assigned to the subject to give the drug. Placebo was used to screen placebos that most closely resembled the appearance, odor, and taste of Ginkgo biloba pills, and placebos were packaged in the same way as Ginkgo biloba pills to minimize the risk of blindness. The experiment was designed with a two-level blind method and blinded concealment was performed at the same time. The first-level blind-end blindness was achieved after researchers completed clinical trials and statistical analysts completed data management. After completing the statistical analysis and obtaining the corresponding conclusions, the secondary blind will be uncovered and eventually form a statistical analysis report.

### 4.7. Combination Therapy

No other blood circulation and blood stasis herbs and hypoglycemic drugs can be taken at the same time during the test. If the patient has existing underlying diseases, such as hypertension and hyperlipidemia, they can be combined according to the relevant guidelines. If angina occurs during the trial, nitroglycerin can be given and the dose, number of uses, and time can be recorded in the case report form.

The medicines that must be taken in conjunction with the disease can remain unchanged. If there are other treatments, the medicine name or other treatment name, dosage, number of uses, and time must be recorded in the case report form.

### 4.8. Efficacy Index

Subjects need to be at baseline, treatment week 8, week 10, week 18, week 20, week 28, week 30, week 38, week 40, week 48, week 50, and week 58 visits. Each visit requires observation and recording of efficacy indicators.

The main evaluation indicators for this trial are the changes in blood glucose and the Seattle Angina Questionnaire (SAQ). The measurement of blood glucose mainly observed the changes of fasting plasma glucose (FPG) and 2 h postprandial blood glucose (2hPG).

The secondary evaluation criteria will be mainly observing the following changes: the incidence of angina symptom scores, C-reactive protein, glycosylated hemoglobin (HbA1c), fasting insulin, blood lipids, metabolomics analysis, and major adverse cardiac and cerebral vascular events (MACCE).

### 4.9. Outcomes

*(1) Primary Outcomes*

*(a) The Changes in Blood Glucose*. The value of fasting blood glucose (FPG) and the value of 2 h postprandial blood glucose (2hPG).

*(b) The Seattle Angina Questionnaire (SAQ)*. The SAQ dose judgment criteria are as follows. The table is divided into 5 items and 19 items: physical activity limitation (PL, question l), angina stable state (AS, question 2), angina pectoris (AF, questions 3-4), treatment satisfaction (TS questions 5-8), and disease cognition (DP, questions 9-11). After scoring the 19 items of the 5 major items one by one, each score is forwarded.

The standard score = (actual score - the lowest score in this aspect)/(the highest score in this aspect - the lowest score in this aspect)×100; the higher the score, the better the quality of life and the functional state of the patient.

*(2) Secondary Outcomes*. They are angina symptom score, C-reactive protein, glycosylated hemoglobin (HbA1c), fasting insulin, blood lipids, metabolomics analysis, and the incidence of composite endpoints of major adverse cardiac and cerebral vascular events (MACCE).

Blood lipids are as follows: cholesterol, triglycerides, high-density lipoprotein, and low-density lipoprotein.

Metabolomics test and analysis: 1 ml of plasma, 2 ml of serum, 5 ml of urine, and 10 g of feces were collected each time. Metabolomic analysis of blood samples, feces, and urine samples was performed to analyze the differences in metabolites between patients taking Ginkgo biloba drop pills and placebo before and after treatment.

Major adverse cardiac and cerebral vascular events (MACCE) include cardiovascular death, nonfatal myocardial infarction, stent thrombosis, revascularization, ischemic stroke, and hospitalization for unstable angina.

### 4.10. Safety Indicators

The safety indicators will include the occurrence of adverse events and serious adverse events, vital signs, and laboratory tests. The subjects were required to have their examination records at baseline, 8 weeks, and 58 weeks of treatment, except for the baseline test during the pregnancy test.

(1) Adverse events and serious adverse events: statistical analysis of the occurrence of adverse events and serious adverse events.

(2) Vital Signs: analysis of blood pressure, respiration, heart rate, and body temperature before and after treatment.

(3) Laboratory tests: including blood routine, urine routine, liver function, renal function, blood lipids, 12-lead ECG, and urine pregnancy test for women of childbearing age; analyzing laboratory tests before and after the test for abnormalities, clinical significance, and test drug relevance.

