## 4. Methods

### 4.1. Trial Design

This is a randomized, double-blind, placebo-controlled, single-case clinical trial in which each subject can be considered as having its own RCT. Twelve subjects with CHD associated with IGR will be screened. Each N-of-1 trial will consist of 3 cycles, including 6 treatment periods, 2 of which are in one group, including 8 weeks of placebo treatment and 8 weeks of Ginkgo biloba. Each subject took Ginkgo biloba drop pills or Ginkgo biloba drop pills simulant at random. There was no washout period at the beginning of the study and there was a 2-week washout period before each treatment period. The entire experimental observation time window is 58 weeks ± 5 days.  Table 1 shows the study design of the subject's medication process. The protocol conforms to the Standard Protocol Items: CONSORT extension for reporting N-of-1 trials (CENT) 2015 [16]. The CENT 2015 checklist can be found in Additional file 2.

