### 4.13. Statistical Methods

Statistical analysis software will use SAS statistical analysis software version 9.4.

The results were analyzed at the end of the test. The description of the quantitative indicators will calculate the mean, standard deviation, median, minimum, maximum, and interquartile range. The description of qualitative indicators will calculate the number of cases and percentage of each category. All statistical tests use two-sided tests. When the* P* value is less than or equal to 0.05, the difference is considered statistically significant (except where specifically stated). Descriptive statistics will be performed on the completion of the study. Demographics and baseline characteristics will be compared between groups to analyze the balance between the groups.

The analysis of efficacy indicators will use Revman5.0 software for meta-analysis.

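### Section 4.10 names only a before/after contrast for vital signs and laboratory tests, which mixes time change with, in expectation, half of any Ginkgo effect

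*Protocol article*

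**What the plan says.** Section 4.10 of the protocol article lists three safety indicators: adverse and serious adverse events, vital signs, and laboratory tests. A contrast is attached to the last two only.

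- Vital signs: "analysis of blood pressure, respiration, heart rate, and body temperature before and after treatment".
- Laboratory tests: "analyzing laboratory tests before and after the test for abnormalities, clinical significance, and test drug relevance".
- Timing: "The subjects were required to have their examination records at baseline, 8 weeks, and 58 weeks of treatment". Table 1 agrees: it marks these examinations at screening, in the first-period column and at week 58.

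On the design, section 4.1 states "Each N-of-1 trial will consist of 3 cycles, including 6 treatment periods", each cycle "including 8 weeks of placebo treatment and 8 weeks of Ginkgo biloba". Section 4.5 randomises in blocks of 2, giving an order of AB or BA in each cycle. Section 4.13 sets a general rule, "When the* P* value is less than or equal to 0.05, the difference is considered statistically significant", without tying it to vital signs or laboratory data.

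The article does name placebo elsewhere. The metabolomics item in section 4.9 sets Ginkgo against placebo as well as before against after.

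**The concern.** In a placebo-controlled trial the safety question for a measured variable is whether it differs between Ginkgo and placebo. A before/after change answers another question: whether the variable moved over time in patients on a mixture of the two treatments. The placebo periods are then pooled with the Ginkgo periods and no longer serve as the control.

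Two errors can follow. A drift over 58 weeks from season, co-medication or disease course can be taken for a drug effect. A real effect on blood pressure, liver or renal function is diluted, and an opposite drift can hide it. Section 4.10 also asks whether laboratory changes are relevant to the test drug, and a pooled before/after change cannot show that by itself.

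**Working it through.** **1. Reproduce the timeline.** Section 4.1 gives six 8-week periods, with "there was a 2-week washout period before each treatment period" but none before the first, so there are five washouts. 6 × 8 + 5 × 2 = 58 weeks, matching "The entire experimental observation time window is 58 weeks ± 5 days"; 6 × 8 = 48 weeks on study medication, matching the abstract. Periods end at weeks 8, 18, 28, 38, 48 and 58. Week 8 therefore closes period 1 and week 58 closes period 6.

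**2. Treatment at the two safety visits.** AB or BA in each of three cycles gives 2³ = 8 sequences. Period 1 is Ginkgo in 4 of the 8, and so is period 6, so the probability is 0.5 at each visit. The two periods carry different treatments in half of the sequences.

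**3. What the pooled change estimates.** Let τ be the time change, δ the Ginkgo minus placebo effect, and q the share of patients who have just finished a Ginkgo period. Without carryover,

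mean before/after change = τ + qδ, with E(q) = 0.5.

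In 12 patients, q is exactly 6/12 with probability 924/4096 = 0.23. It lies between 3/12 and 9/12 with probability 1 − 2(1 + 12 + 66)/4096 = 0.96. Half is thus an expectation; the realised weight could plausibly be 25% to 75%.

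**4. Illustration of size.** The article gives no SD, correlation or test for these data. Assumed here: outcome SD 1; within-patient correlation r of 0.5, 0.7 or 0.8; linear drift reaching the stated amount at week 58; two-sided 5%. Before/after is a paired t test of baseline against week 58. The treatment contrast is a model with patient, visit and treatment effects over all three visits (21 residual degrees of freedom).

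For drift alone, the SD of the change is √(2(1 − r)) = 1.00, 0.77 and 0.63. The non-central t distribution with 11 degrees of freedom and non-centrality 0.5 × √12 / SD gives the first row. The other entries are simulated (20,000 trials each).

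| Scenario | Before/after rejects (r = 0.5 / 0.7 / 0.8) | Treatment contrast rejects |
|---|---|---|
| Drift 0.5 SD, no drug effect | 35% / 53% / 70% | 5% / 5% / 5% |
| Drug effect 0.5 SD, no drift | 12% / 17% / 21% | 25% / 39% / 54% |

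With a drug effect of 1 SD and no drift, the mean before/after change was 0.50 and the treatment contrast averaged 1.00.

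**5. What the existing visits can support.** In expectation 12 × 0.5 = 6 patients are examined once on each treatment, 58 − 8 = 50 weeks apart. The others contribute mainly through comparison between patients at the same visit.

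**The case against.** The strongest reply is that section 4.10 prescribes no test. Its laboratory wording fits a result-by-result clinical review of abnormal values, and tabulation by treatment could sit in an analysis plan that is not shown. This stands in part. The rejection rates above describe an assumed test, and nothing in the article says that a non-significant result would be taken as proof of safety. What remains is that before/after is the only contrast the text names for these two items, and what a pooled change estimates does not depend on any test.

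Second, the vital-signs item speaks of treatment, not of the whole trial, and could mean within a period. That is a fair reading, but no safety examination is scheduled at the start of period 6. Only period 1 could be handled that way, and baseline to week 8 pooled over patients still mixes the two treatments.

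Third, a power comparison can flatter the remedy. The before/after test above uses one post-baseline visit and the model uses two. For a 1 SD effect without drift, using week 58 alone, before/after detects about 29% / 41% / 49% and a by-treatment comparison of changes about 34% / 49% / 66%. With both visits on each side the figures are about 39% / 55% / 68% and 73% / 90% / 97%. The advantage is real but depends on using both visits.

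A reader might also infer that the trial cannot answer its safety question, or that before/after would be wrong however many visits were added. The documents support neither. Adverse and serious adverse events are a separate indicator without a before/after contrast, section 4.11 counts laboratory abnormalities among adverse events, and Table 1 has blood lipids measured in every period. Before/after changes taken within each period and labelled by treatment would be an ordinary crossover comparison.

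**Conclusion.** The point holds, limited to vital signs and laboratory tests. The only contrast stated for them does not match the placebo-controlled design. Pooled over patients, it estimates time change plus, in expectation, half of the Ginkgo effect, with a realised share of 25% to 75% with probability 0.96 in 12 patients. Drift of 0.5 SD alone would make a before/after test reject in roughly a third to 70% of trials under the assumed correlations.

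This rests on independent random order in each cycle, no carryover and no cumulative effect. By week 58 every patient has had 3 × 8 = 24 weeks of each treatment, so harm that builds up and persists would appear in the before/after change and not in the week-58 treatment contrast. That is a reason to keep the before/after summary as description.

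**What to change.** Amend section 4.10 (2) and (3) along these lines: *Each week-8 and week-58 result is classified by the treatment of the period just completed. The Ginkgo minus placebo difference is estimated with its 95% confidence interval from a model with patient, visit and treatment effects, with baseline as the pre-treatment visit. Newly abnormal results are tabulated by treatment. Before/after summaries are descriptive, and no conclusion of safety is drawn from P > 0.05.*

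The cost is a few sentences and a little more analysis, with no new visits, samples or patients. The drawback is precision. With about half of the 12 patients examined on both treatments, intervals will be wide, and even this contrast misses a 0.5 SD effect about 75% / 62% / 47% of the time at correlations of 0.5 / 0.7 / 0.8. The protocol should state that limit beside the analysis.

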### 4.11. Adverse Events

*(1) Adverse Events (AE)*. Definition: A patient or clinical trial recipient receives a drug after an adverse medical event but does not necessarily have a causal relationship with the treatment. Thus, an adverse event refers to any unanticipated signs associated with the use of a medical (study) product, including laboratory abnormalities, symptoms, or conditions, whether or not medical (study) products are considered. Thus, an adverse event refers to any unanticipated signs associated with the use of a medical (study) product, including laboratory abnormalities, symptoms, or conditions, whether or not medical (study) products are considered.

*(2) Serious Adverse Events (SAE)*. Definition: Severe adverse events refer to the following adverse events at any dose of the test drug or at any time during the observation period, including hospitalization, extended hospital stay, disability, work ability, life-threats or death, and congenital malformations.

*(3) Judgment of Causal Relationship between Adverse Events and Test Drugs*. Adverse reaction evaluation criteria (including symptoms, signs, and laboratory indicators) are as follows.

(1) The time of adverse reactions coincides with the time of administration.

(2) Adverse reactions are associated with known adverse effects of the drug.

(3) Adverse reactions cannot be explained by other reasons.

(4) The adverse reactions are alleviated or disappeared after stopping the drug.

(5) Adverse reactions are reproduced after administration.

*(4) Judgment Criteria for Adverse Events and Drug Relationships*. (1) It is definitely related to: the reaction appears in a reasonable time sequence according to the medication, and it is consistent with the type of reaction known to the suspected drug. The reaction disappears after the suspected drug is stopped, and the patient's clinical state or other reasons are unlikely to produce the reaction.

(2) It may be related to: the reaction appears in a reasonable time sequence according to the medication, and it is consistent with the type of reaction known to the suspected drug. The reaction can be alleviated after the suspected drug is stopped, but the patient's clinical state or other reasons may also produce the reaction.

(3) It may be irrelevant: the reaction appears to be inconsistent with the reasonable time sequence after administration and does not meet the type of response known to the suspected drug. The response is not alleviated after the suspected drug is discontinued, and the patient's clinical state or other causes may cause the reaction. The response is reduced after the state is improved or after other reasons are eliminated.

(4) It must be irrelevant: the reaction does not meet the reasonable time sequence after administration and does not meet the type of reaction known to the suspected drug. The clinical state of the patient or other reasons can produce the reaction, and the response is relieved after the disease state is improved or other causes are eliminated.

(5) It cannot be judged that there is no clear relationship between the occurrence of the reaction and the time sequence after administration, and the type of reaction known to the drug is similar, and other drugs used at the same time may cause the same reaction.

It is certain that it may be relevant, may be related, and cannot determine three adverse reactions that can be considered as drugs.

*(5) Observation and Recording of Adverse Events*. Subjects with AE should be followed up until the AE recovers (returns to normal or to baseline), or until the condition is stable, or until there is a reasonable explanation.

For AEs that have not recovered at the end of the observation period or AEs that were known at the last visit during the observation period, the investigator should follow up after the visit to return to the above satisfactory results. The necessary treatment, reports, and records should be given as required. For any exceptions, you must go through the consent of the sponsor's security management contact.

*(6) Records and Reports of Serious Adverse Events*. In case of serious adverse events during the trial, the unit undertaking the clinical trial shall immediately take the necessary measures to protect the safety of the subject and report to the local provincial drug regulatory authority and the State Food and Drug Administration, the sponsor within 24 hours. The clinical trial is responsible for the unit ethics committee and informs the participating units. The sponsor will ensure that the reporting procedures for all legal and regulatory requirements are met.

The SAE collection time for this study ranged from 30 days after the signed informed consent to the last use of the study drug.

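### The causality scale in section 4.11(4) has no grade for a plausibly timed reaction of a type not already known for Ginkgo, so such an event cannot be counted as an adverse drug reaction

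*Protocol article*

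**What the plan says.** Section 4.11(4) of the protocol article prints five causality grades in full.

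- **Grades (1), definitely related, and (2), possibly related**, open with the same double condition: "the reaction appears in a reasonable time sequence according to the medication, and it is consistent with the type of reaction known to the suspected" (that is, the study medication). They then differ. Grade (1) adds: "The reaction disappears after the suspected drug is stopped, and the patient's clinical state or other reasons are unlikely to produce the reaction". Grade (2) adds: "The reaction can be alleviated after the suspected drug is stopped, but the patient's clinical state or other reasons may also produce the reaction".
- **Grade (3), possibly irrelevant**, applies when "the reaction appears to be inconsistent with the reasonable time sequence after administration and does not meet the type of response known to the suspected" (again, the study medication), the event does not improve on stopping, and another cause is possible. **Grade (4), certainly irrelevant**, has the same two opening conditions on timing and type and also names another cause.
- **Grade (5), not assessable**, needs an unclear time relationship, and in addition "the type of reaction known to the drug is similar, and other drugs used at the same time may cause the same reaction".

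A closing sentence, poorly worded, names three grades that count as drug reactions. The natural reading is (1), (2) and (5).

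Just before this, section 4.11(3) lists five considerations for judging causality. Agreement with known effects is one of them and reappearance on re-administration is another. No rule connects that list to the five grades.

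**The concern.** In all three grades that appear to count as drug reactions, a known or similar reaction type is a necessary condition. Both irrelevant grades need implausible timing. An event that starts plausibly on treatment but is of a type not yet known for Ginkgo falls between them. An investigator who follows the text can neither call it related nor call it irrelevant.

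The design makes this more than a formality. Under section 4.1 each subject has three cycles, each with one 8-week Ginkgo period and one 8-week placebo period, with 2-week washouts between periods. The first Ginkgo period is therefore followed by two planned re-exposures. Recurrence over those periods would be informative about a new reaction, yet no grade in 4.11(4) uses it.

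At stake is the causality attribution of individual events, including the judgement of test-drug relevance that section 4.10 asks for in laboratory findings, and any count of adverse drug reactions built on it.

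**Working it through.** The plan gives no figure to reproduce, so the check is to set the five definitions side by side and see which events they cover.

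**Inputs**, all from section 4.11(4):

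| Grade | Timing | Type known or similar | Improves on stopping | Other cause | Counted as drug reaction |
|---|---|---|---|---|---|
| (1) | plausible | yes | yes | unlikely | yes |
| (2) | plausible | yes | yes | possible | yes |
| (3) | implausible | no | no | possible | no |
| (4) | implausible | no | not stated | yes | no |
| (5) | unclear | yes | not stated | yes (other drugs) | yes |

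**Coding.** Timing has 3 levels. Known type, improvement on stopping and alternative cause each have 2. This gives 3 × 2 × 2 × 2 = 24 profiles. Disappearing and being alleviated on stopping are both coded as improvement. Where a grade does not state a feature, either value is accepted.

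**Results.**

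- Plausible timing, unknown type: 2 × 2 = 4 profiles, and 0 of the 4 have a grade. This includes the profile that improves on stopping and has no other cause.
- Unknown type at any timing: 3 × 4 = 12 profiles. None reaches a counted grade. Two (implausible timing with another cause) reach grade (4), one of which also meets grade (3). The other 12 − 2 = 10 are ungraded.
- Whole scale: 6 profiles have a grade and 24 − 6 = 18 do not. The gaps include known-type events, such as a plausibly timed known reaction that does not improve on stopping.

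**Which condition blocks the grade.** Take a plausibly timed event of unknown type that improves on stopping and has no other cause. It misses grade (1) on type alone. It misses (3) on timing, response to stopping and other cause, (4) on timing and other cause, and (5) on timing, type and other drugs. If another cause is possible, it misses (2) on type alone and (4) on timing alone.

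**Dependence on the closing sentence.** The result for plausible timing does not rest on reading that sentence as (1), (2) and (5). An event without a grade cannot be counted, whichever grades count.

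**The case against.** The strongest reply is that little depends on this scale. Section 4.10 names the occurrence of adverse events and serious adverse events as the safety indicator, together with vital signs and laboratory tests. It names no adverse-reaction rate. Section 4.11 follows up all adverse events, and the 24-hour reporting of serious events has no causality condition. Occurrence can also be compared between blinded Ginkgo and placebo periods within a patient without any grading. All of this stands, and it confines the point to attribution.

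A second reply is that with 18 of 24 profiles ungraded, the grades read as typical descriptions rather than an algorithm, and that 4.11(3) treats known type as only one of five considerations. An investigator could sensibly choose grade (2) or (5). That is likely in practice, but it departs from the printed conditions, and because nothing links 4.11(3) to the grades, the choice is left to each assessor.

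Three stronger readings are tempting, and the document does not support them:

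- **Known reactions are not adverse events at all**, because the definition says "an adverse event refers to any unanticipated signs associated with the use of a medical (study) product". The same section lists known adverse effects among its causality considerations and grades events of known type, so it plainly treats them as adverse events.
- **The main safety outcome is compromised.** Section 4.10 does not support this, as above.
- **New reactions will be pushed into the irrelevant grades, so the adverse-reaction count is biased downward.** This is not shown. With no other cause, the event lies closer to grade (1) than to (3) or (4). With another cause possible, it is one condition away from both (2) and (4). The direction depends on how assessors improvise.

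**Conclusion.** The point holds in a limited form. As printed, a plausibly timed reaction of a type not already known for Ginkgo has no causality grade and cannot be counted as an adverse drug reaction, even if it resolves on stopping and recurs in later Ginkgo periods. That is 4 of 4 such profiles. More broadly, 0 of 12 unknown-type profiles reach a counted grade. These are counts of combinations, not event frequencies. The document gives no basis for saying how often such events would occur.

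The conclusion rests on applying the definitions as written. The 0-of-12 result also assumes that the closing sentence means grades (1), (2) and (5). Recording, follow-up and analysis of adverse and serious adverse events, and both primary outcomes, are unaffected. Because the rule is printed in full, this is a flaw in what the article states rather than detail left to another document. It is worth correcting because the correction costs very little.

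**What to change.** Revise section 4.11(4) so that every combination of timing, type, response to stopping and alternative cause falls in exactly one grade:

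- In (1), (2) and (5), make a known reaction type a supporting condition, not a necessary one.
- In (3) and (4), drop unknown type as a requirement, and state that plausible timing alone does not rule out these grades when another cause better explains the event. Without the second step, a well-timed, unknown-type event with a better explanation would still have no grade. State one feature that separates (3) from (4), since one profile now meets both.
- Let recurrence on re-administration, already listed in 4.11(3), inform the grade. Because investigators stay blinded until completion (section 4.5), record recurrence by period and read it against the allocation once that is known.
- Restate the closing sentence so that the counted grades are named by number.

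An ordered rule is one way to guarantee a single grade. If another cause explains the event better, use (3) or (4). Otherwise, if timing is implausible, use (3); if unclear, use (5). If timing is plausible, use (1) when the event disappears on stopping, no other cause is likely, and either the type is known or the event recurred; use (2) in all remaining cases.

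The cost is a wording change in section 4.11 and the case report form guide, with no extra visits or tests. The adverse-reaction count may come out slightly higher.
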